### Posttraumatic stress following childbirth

In a meta-analysis, the prevalence for PTSD following childbirth (PTSD FC) was 3.1% among community samples and 15.7% among high-risk samples (e.g. pregnancy complications, emergency caesarean section, preterm birth) [6]. In a more recent review [7], the estimated prevalence was 2.4% among community samples, and 4.9% including both community plus high-risk samples when controlling for previous PTSD. The prevalence for clinically significant post-traumatic stress symptoms ranged between 9.6 and 27.3% [7]. The variation in prevalence rates may be explained by the timing and method used for assessment of PTSD criteria and symptoms [6, 7]. Prevalence rates were consistently higher in both studies when assessed close to childbirth. The prevalence rates above are based on the fourth edition of the Diagnostic and Statistical Manual for Mental Disorders (DSM-IV-TR) [8]. There is no sub-clinical or partial PTSD diagnose in DSM-IV, which is reflected in the heterogeneity regarding definition and label of clinically significant post-traumatic stress symptoms.

The definition of stressors for the development of PTSD according to DSM-IV can be applied to posttraumatic stress FC. A diagnosis of PTSD required affirming the following criteria: the stressor criterion (A) included stressful situations in which a person experience, witness, or is confronted with an event that involves actual death or threat of death or serious injury, or a threat to the physical integrity of self or others; the three symptom criteria re-experiencing (B), avoidance (C), and increased arousal (D); the duration criterion (E), and the influence criterion (F). Several risk factors are associated with PTSD FC, such as psychological factors (e.g. fear of childbirth), prepartum and partum factors (e.g. type of delivery) and postpartum factors (e.g. poor coping) [6, 9]. In a systematic review, five categories of risk factors for PTSD FC are identified: negative perception of childbirth, maternal mental health, history of trauma and PTSD, delivery mode and complications, and low social support [7].

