The current study addresses gaps concerning treatment for this population. First, the intervention consists of two steps, where step-1 is offered to all women with negative birth experiences, regardless of whether they have a PTSD diagnose or not. Those who fulfil the criteria for PTSD FC after step-1 are offered step-2. Second, the partners are invited to join the treatment in step-1. We also include long-term follow ups. The study involves the partner by facilitating a shared treatment experience with the mother, giving information on how to support her emotionally, and providing practical support that may help her to get the greatest benefit from the treatment program. Finally, we will present a health economic evaluation.

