### Hypothesis

#### Primary

Women who report a negative experience from childbirth and receive iCBT+TAU will report lower levels of posttraumatic stress and depressive symptoms, as well as a smaller proportion of participants classified as fulfilling the criteria for PTSD, and a smaller proportion of participants with postpartum depression according to cut-off compared with those receiving only TAU.

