Before discharge from hospital, women rate their overall childbirth experience on a paper and pencil administered Likert-scale (range; 0–10), please see Figure 2. Those with a low rating on the childbirth experience, defined as ≤5 on the Likert scale, and/or exposure to an immediate caesarean section and/or a major bleeding (≥2000 ml) following childbirth (see material section) are asked to consider participation in the study. Immediate caesarean section, is defined as when used for life-threatening situations for either the baby or the mother. About 8 weeks postpartum the women are contacted and informed about the study via telephone. To those interested in participation, information and consent is sent home by mail and to those not responding to contact after three attempts. Partners are also invited to participate at the same time as the mother and they sign the same consent form after reading the information about the study. Participants who consent are provided with login details to the Internet study site. The login and reporting procedures are as follows: Each login requires double authentication. At the first login, participants respond to baseline measures after which they are randomly allocated to either TAU or iCBT+TAU. They are immediately informed about the allocation via an email from the web portal. The partners are allocated together with the mothers. iCBT-1 + TAU and TAU are initiated immediately after randomisation. Participants respond to the questionnaires after iCBT step-1 (at 6 weeks) and after iCBT step-2 (at 14 weeks) followed by measurements annually up to 4 years post treatment. The U-CARE platform automatically sends reminders via email and text messages when measurements are not completed within 14 days. After another 7 days, participants are reminded via a telephone call. Paper copies of the questionnaires will be sent by mail to unresponsive participants. Reminders are also sent to those who delay their initiation of iCBT treatment and when participants delay the weekly treatment modules.

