### Interventions

#### iCBT step-1 + TAU

The first step of the intervention encompasses iCBT with therapist support at request. Participants can read the material and/or choose to listen to an audio-visual presentation as well as viewing videos covering e.g. breathing retraining and vignettes of childbirth stories. It also includes psychoeducation and basic interventions and techniques that aim to improve health and alleviate symptoms caused by posttraumatic stress and depression [46] (Table 1). The six weekly modules include homework based on the content. The partner receives identical content and a ‘partner instruction’ with specific tasks to perform (support and make room for practice; reflective listening; talk about the birth experience and present symptoms etc.) A psychologist guide, encourage, and respond to questions from the participants. After the completion of each module the psychologist writes an email to the participant to inform her that the week’s CBT is completed. Participants will be informed on a regular basis that they may ask questions or consult the psychologist via email.

**Table 1 Tab1:** Overview of the of the iCBT step-1 week by week for the woman and her partner

	Woman	Partner
Week 1	Information, psychoeducation, breathing retraining	Take part of the material, facilitate, make time, homework reminder
Week 2	Vignettes, common symptoms, fear and avoidance	Discuss the information, remind and encourage practicing
Week 3	Depressive symptoms, significance of relations,“ reflective listening”	Reflective listening, encourage talk about childbirth, remind/encourage practice
Week 4	Exposure, talking about the childbirth	Watch pictures & movies, talk about the experiences, support practice
Week 5	Managing anxiety and depressive symptoms, psychological health, values, recovery	Talk about values, psychological health, and relaxing high demands
Week 6	Summary, repetition and relapse prevention	Talk about the information, make time to summarize, maintenance plan

Note. The content is identical for the partner and the mother except that the partner has additional information with instructions on what to do, discuss, facilitate etc

^1^Every week contains homework assignments based on the content of the module

The women who complete iCBT step-1 and fulfil the criteria for PTSD (according to The Traumatic Event Scale) will be offered iCBT step-2.

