### Primary outcome measures

*The Traumatic Event Scale (TES)* measures post-traumatic stress symptoms related to childbirth, 3 months after delivery [50]. The scale was developed to assess the DSM-IV [8] criteria for PTSD FC. It comprises the stressor criterion A, with the four items formulated as follows; 1) The childbirth was a trying experience, 2) The childbirth was a threat to my physical integrity, 3) During the childbirth I was afraid that I was going to die, 4) During the childbirth I felt anxious/helpless/horrified. The response options for the A criterion are “not at all, somewhat, much, very much”, The A criterion is met if the alternatives “much” or “very much” is chosen on item 1, 2 or 3, and 4. The three categories of PTSD symptoms (in total 17 items) assess re-experiencing (B-criterion), avoidance (C-criterion), and arousal symptoms (D-criterion). The response options for these three categories are “never/ not at all, rarely, sometimes, often” and to be accounted for as presence of a symptom, the alternatives “sometimes” or “often” are required. In accordance with the DSM-IV one of five B items, three of seven C items, and two of five C items are required to fulfil the criteria respectively. The duration criterion (E) is fulfilled if symptoms have been present for 1 month at least. The influence criterion (F) is met if the degree to which it influenced life was ≥ 6 with regard to at least one of the symptoms. The 17 symptom criteria are summed and higher score indicate higher prevalence of symptoms. The symptom scores have shown good internal reliability (*α* = .84) and split half reliability (.90). The difference between the two study arms as concerns the proportion of participants classified as fulfilling the criteria for PTSD at all assessment points will be reported. Means for the summed symptoms score (criteria B, C, and D) will be compared between the study arms. The TES has been adapted for this particular traumatic event (childbirth) where questions point directly at the childbirth [50]. The scale has been developed and evaluated in a Swedish context and thus is considered clinically relevant.

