### Statistical analysis

Data will be imported from the U-CARE web portal. For demographic data, χ^2^ and t-test will be used to examine differences between the groups at baseline. For the continuous data, a mixed model repeated measure (MMRM) will be used to evaluate treatment effects. All available data from all participants are used so this will be a suitable approach for intent-to-treat analysis. Effect sizes (Cohen’s *d*) will be based on suggestions for repeated measures and multi-level designs [72, 73] and effect sizes for planned contrasts for interactions [74]. For the binary outcome data *χ*^2^ analysis and calculations of odds-ratios will be performed. Per-protocol (defined as a minimum of four completed weeks out of six in step-1 and a minimum of six completed weeks out of eight in Step-2), completer, and drop-out analysis will be performed. Exploratory sub-group analyses will be performed between those with negative birth experience, immediate caesarean section and those with a major postpartum haemorrhage. We will also investigate differences between primiparas and multiparas, those with/without vacuum extraction, those with/ without partner involvement, as well as those with/without pro-longed labour. We will also consider known risk factors for PTSD FC as covariates.

During the study period, data from all mothers giving birth at the four trial sites will be collected from their patient records. In order to describe and compare our sample with this population we will collect a) obstetric data, b) an additional rating of overall childbirth experience and c) EPDS. The additional rating of overall childbirth experience and the EPDS is assessed at the first visit to maternal care after the birth (approximately 6–8 weeks). Subgroup investigations will be performed among those who; declined participation but were eligible, did not respond to the invitation but were eligible, were eligible but not invited (missed) and all who rated overall childbirth experience. Finally, we will report reasons for not participating among those who consented but did not participate. Statistical analyses will be performed by SPSS (IBM SPSS Statistics).

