## Discussion

Most women with negative experiences and PTSD FC have the ability to handle the psychological stress it may cause, but in previous studies a significant proportion of women have reported symptoms of posttraumatic stress, anxiety and depressive symptoms that need attention. However, little is known about how to treat psychological reactions in women with negative experiences from birth and it is unclear how symptoms are perceived and how they develop over time. For these reasons there is a growing recognition of the need to offer interventions for those suffering from mental illness related to reproductive events, and at the same time there is almost no published research on treatment for PTSD FC. To the best of our knowledge, only one RCT has examined the effect of iCBT for women with PTSD [42]. This study showed good outcome at the end of treatment for iCBT compared with a wait list condition. It is however uncertain whether trauma focused treatment for PTSD caused by events other than childbirth are suitable for those with negative experiences FC, and whether the long-term effects are beneficial for those with PTSD FC.

It is of particular importance to consider the recruitment process in clinical trials. In our study, the majority of the women in the participating study-centres rate their overall childbirth experience as part of the standard protocol at these centres. We contact all women with a low rating and believe that we address a majority of the women with a negative experience FC who have a potential need for psychological follow up. In our study we offer minimal therapeutic support which may affect compliance from the participants. We also know that people with trauma-related psychological problems often display avoidant behaviour and therefore some women may be reluctant and not motivated to accept offered psychological treatment.

Findings in this study will contribute knowledge and understanding of women with negative birth experiences and PTSD FC. The study will yield information about the psychological status in this group and a better understanding of potential cost-effective interventions that could improve women’s psychological health and quality of life. Hopefully this might reduce health care costs and promote positive bonding/relationship to the child and partner.

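### The per-protocol rule includes a step-2 threshold that only iCBT women with PTSD after step 1 can face, so a whole-arm comparison based on it would select on a primary outcome in one arm (supportive analysis only; minor)

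*Protocol article*

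**What the plan says.** The Statistical analysis section lists a per-protocol analysis beside completer and drop-out analyses and gives its rule in one parenthesis: "defined as a minimum of four completed weeks out of six in step-1 and a minimum of six completed weeks out of eight in Step-2". It does not say how the two thresholds combine for a woman who is never offered step 2, nor whether TAU is restricted in any way.

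Entry to step 2 is stated twice. The intervention section reads: "The women who complete iCBT step-1 and fulfil the criteria for PTSD (according to The Traumatic Event Scale) will be offered iCBT step-2". The Background reads: "Those who fulfil the criteria for PTSD FC after step-1 are offered step-2". TAU has no steps.

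PTSD status is also an outcome. The primary hypothesis predicts "a smaller proportion of participants classified as fulfilling the criteria for PTSD" under iCBT, and the Primary outcome measures section says that the difference between arms in the "proportion of participants classified as fulfilling the criteria for PTSD at all assessment points will be reported". The summed TES symptom score is compared between arms as well. On timing, the Procedure section says: "Participants respond to the questionnaires after iCBT step-1 (at 6 weeks) and after iCBT step-2 (at 14 weeks".

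The main analysis of continuous outcomes is a mixed model for repeated measures (MMRM) on all available data, presented as intention-to-treat, with effect sizes for interaction contrasts. Binary outcomes are analysed by chi-square test and odds ratio.

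**The concern.** A per-protocol comparison should drop women for not taking the treatment, not for how they scored on the outcome. Here the second threshold exists only for women who were PTSD-positive after randomisation, and only in the iCBT arm. A TAU woman with PTSD at week 6 stays in the comparison whatever she does. An iCBT woman with the same status may have to complete six further modules to be counted. At week 6 the rule would also condition on treatment not yet delivered.

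The direction of the bias depends on a choice that the text leaves open. If that choice were made after the data were seen, the per-protocol result could neither support nor question the main result.

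**Working it through.** **The three readings**

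1. *Step-2 threshold only for women offered step 2.* A woman without PTSD at week 6 needs one threshold and a woman with PTSD needs two. Women with PTSD are lost selectively from iCBT, which favours iCBT.
2. *Both thresholds for everyone.* Only women with PTSD at week 6 can qualify. At week 6 the iCBT set is 100% PTSD by construction, which runs against iCBT.
3. *One threshold per step.* The week-6 set has no step-2 filter and no bias from this rule. The step-2 set consists only of women who had PTSD at week 6, and no matching TAU group is stated.

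**Inputs**

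- From the article: planned effect d = 0.5 and a total of 130 (65 per arm). A two-sided noncentral t calculation gives 64 per arm (128), and power 0.808 at 130, so the stated figure reproduces; it is used here only as a yardstick.
- Week-6 PTSD proportion p: 15.7% (high-risk samples) or 4.9% ("4.9% including both community plus high-risk samples when controlling for previous PTSD"). Both come from the Background. Applying them to trial women after step 1 is an assumption.
- c, the share of women with PTSD and at least four step-1 weeks who are offered step 2, and q, the share of those offered who reach six of eight weeks. The article gives neither. I use c = 1 and q = 0.7, 0.5, 0.3.
- No true effect; step-1 adherence unrelated to PTSD; TES treated as normal with PTSD as its top p; all correlations between baseline, week 6 and week 14 equal to 0.6. All are assumptions.

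**PTSD proportion, reading 1**

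Week 6: the share of women with PTSD who are kept is (1 - c) + cq = 1 - c(1 - q). The iCBT odds are p[1 - c(1 - q)]/(1 - p), against p/(1 - p) in TAU. The odds ratio is therefore **1 - c(1 - q)** at any prevalence, and equals q only if c = 1.

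- c = 1, q = 0.5: odds ratio 0.5. At p = 0.157 the iCBT proportion is 0.0785/(0.0785 + 0.843) = 8.5%, against 15.7%.
- c = 0.7 (illustrative), q = 0.5: 1 - 0.7 x 0.5 = 0.65.

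Week 14, c = 1: under a bivariate normal with correlation 0.6 and p = 0.157, 7.15% of women have PTSD at both visits. At q = 0.5 the iCBT proportion is (0.157 - 0.5 x 0.0715)/(1 - 0.0785) = 13.2%, and the odds ratio is (0.132/0.868)/(0.157/0.843), about 0.81.

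| Week-14 odds ratio | q = 0.7 | q = 0.5 | q = 0.3 |
|---|---|---|---|
| p = 15.7% | 0.89 | 0.81 | 0.73 |
| p = 4.9% | 0.92 | 0.86 | 0.80 |

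**TES score, reading 1, c = 1, q = 0.5**

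The mean of the top 15.7% is 1.531 SD. The raw week-6 shift is -0.0785 x 1.531/0.9215 = -0.130 SD. The shift at baseline and at week 14 is 0.6 x -0.130 = -0.078 SD each. Selection on week-6 score thus also lowers the baseline mean, and a contrast over time removes part of the shift:

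- Change from baseline: week 6, -0.130 + 0.078 = -0.05; week 14, -0.078 + 0.078 = 0.00.
- Baseline-adjusted: week 6, -0.130 + 0.57 x 0.078, about -0.09 (0.57 is the slope fitted after selection); week 14, -0.078 + 0.6 x 0.078 = -0.03.

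At p = 4.9% the raw shifts are -0.052 and -0.031 SD. The change-score values are -0.052 + 0.031 = -0.02 and 0.00.

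**Numbers of women**

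With 70% step-1 adherence (assumed) and q = 0.5, a set that requires step 2 holds 65 x 0.7 x 0.157 x 0.5 = 3.6 women, or 1.1 at p = 4.9%. Reading 1 removes the same numbers from about 45 step-1 adherers.

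**The case against.** The strongest reply is that a condensed article need not spell out its analysis sets. Nothing in it says that the joint rule will be used for the whole-arm contrast, and with one assessment after each step, one threshold per step is a natural reading. Much of this stands. Reading 3 is plausible and harmless at week 6, and reading 2 leaves so few women that it is unlikely to be intended. But the article did write down a definition, and that definition sits badly with its own stepped design. This is more than missing detail.

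Second, a reader might take the raw week-6 shift of -0.13 SD as the size of the TES bias. A single-visit t-test with q = 0.5 and 15.7% PTSD would then falsely favour iCBT in 9.2% of trials instead of 2.5%. The article does not support that inference, because it plans MMRM with interaction contrasts. A change-from-baseline stand-in for that contrast brings the rate to 4.4% at week 6 and 2.5% at week 14. The PTSD odds ratio has no such protection.

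Third, an odds ratio equal to q is not general. If completing step 1 means all six modules, women with PTSD and four or five weeks are never offered step 2 and stay in under reading 1, which moves the ratio towards 1.

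Fourth, few women are involved, and neither adherence nor prevalence has a source in this trial's population. That is correct, and it limits the finding.

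**Conclusion.** The point holds, and it is minor. Used for the whole-arm comparison, the joint per-protocol rule selects on a primary outcome in one arm, either by removing women with PTSD from iCBT or by keeping only them. Read as one threshold per step, what remains is an unmatched TAU comparator for the step-2 set.

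The effect is clearest for PTSD proportion: a null odds ratio of 1 - c(1 - q) at week 6, which is 0.5 at c = 1 and q = 0.5, and about 0.81 at week 14 with 15.7% PTSD. The TES bias under the planned contrast is at most about 0.09/0.5 = 18% of the planned effect at week 6 in that scenario, and close to nil at week 14. There is no bias from this threshold if everyone offered step 2 reaches six weeks. The article gives some reason to doubt that, noting that "people with trauma-related psychological problems often display avoidant behaviour".

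A reader might infer that the trial's main result is compromised. It is not: the intention-to-treat MMRM uses all available data, the sample size is untouched, and no conclusion is tied to the per-protocol analysis.

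**What to change.** - For the week-6 whole-arm comparison, define the per-protocol set by the step-1 threshold alone (at least four of six weeks).
- Preferably use the same set for later whole-arm comparisons. Report step-2 adherence separately: numbers offered, started, and reaching six of eight weeks.
- If a step-2 per-protocol comparison is wanted, compare it only with TAU women who met TES PTSD criteria at week 6, and label it exploratory.

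The cost is a sentence or two in the analysis plan. No new data are needed: treatment is delivered through the study platform, and TES is collected from all mothers at week 6.

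There are two downsides. From week 14 on, the set will include some women who took little of step 2, so its use there is partly a matter of preference. Ordinary selection by step-1 adherence also remains. If women with PTSD are 0.8 times as likely to reach four weeks, the null week-6 odds ratio is 0.80 under the proposed rule, against 0.8 x 0.5 = 0.40 under reading 1 with c = 1 and q = 0.5.
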